**j. Efficacy:**

**A)** **Primary Outcomes:**

1. Mean time (days) for clinical recovery [Day of randomization to the day of clinical recovery (see criteria below)]
2. Proportion of patients showing ‘clinical recovery’

Criteria of ‘Clinical Recovery’:

1. Normal body temperature (≤36.6°C axilla or ≤37.2 °C oral)
2. Absence of cough or mild cough (infrequent, short episodic, non-wheezy, relieved by minimal or no medication, not interfering with routine speech and not related to lying in bed, mild sore throat or nasal congestion)
3. Absence of breathlessness on routine daily self-care chore or respiratory rate less than 30 breaths per minute without supplemental oxygen
4. Absence of any other symptom/sign attributed to COVID-19 illness
5. Normalization of SpO2 by standard peripheral oximetry device (above 95 percent)
6. Recovery should be sustained for at least 48 hours under physician observation
7. Assessed by physician blinded to treatment allocation (blinded end-point assessment)
8. All of the above criteria ought to be fulfilled

Note: Clinical recovery would be deemed from the first day of satisfying the above criteria

**B)** **Secondary Outcomes:**

1) Rate of patients with negative SARS-CoV-2 on nasal or throat swab in a 2 day continuous real time RT-PCR test beginning from ‘first day of clinical recovery’ or ‘Day 10 after onset of symptoms depending on whichever of the two time points is first achieved

2) Timelines (days counted from onset of illness)- normal body temperature, absence or minimal cough (see ‘clinical recovery’ for the definition), absence of dyspnoea, onset of clinical pneumonia, pneumonia diagnosed on chest X-Ray or CT scan, time to supplemental oxygen, admit in intensive care unit, mechanical ventilation (non-invasive), mechanical ventilation (invasive), steroid use, respiratory failure, adult respiratory distress syndrome, cytokine storm syndrome, secondary infection, shock, septicaemia shock, hospital discharge, negative nose or throat swab confirmatory test, and all-cause mortality.

3) Proportion of patients developing an event that reflects clinical or otherwise improvement of worsening (the events are similar to those listed under Timelines, see above)

4) Improvement on pulmonary function tests using simple ‘home expiratory spirometer’ device and peripheral pulse oximetry

5) Improvement in selected laboratory parameters: blood haemoglobin, differential and total leukocyte counts, liver enzymes, renal functions, acute phase reactants, serum IL-6 and other selected cytokines, serum muscle enzymes (CK, CPK), serum ferritin, serum d-Dimer, anti-oxidant markers, serum BNP (cardiac function)

6) Serological Protective Antibody Assay (IgM and IgG)

7) Radiological Improvement on digital chest X - ray and HRCT chest

8) Drug related: side effects and toxicity, and tolerability (Safety criteria: All adverse events occurring during the study will be recorded and monitored as per GCP-ICH guidelines. Safety would also be assessed in case of all withdrawals.)

9) Health status: WHO QOL brief, health related behaviour habit and fitness questionnaire based on visual analogue scale

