**f. Study design:**

This is a prospective, randomized, open label, blinded end point (PROBE), parallel efficacy, multicentric, two arm study to compare the efficacy of a combination of Standard of Care (SOC) plus a selected individual Ayurveda herbal drug (Samshamani Vati Plus or AYUSH 64 or Yashtimadhu) to SOC (active control). The Ayurveda drug is being considered as an adjunctive or an add-on therapy and each of the three drugs will be evaluated in separate two arm trial with a common study design. The drug trials are ‘exploratory’ in design. The Study Flow diagram summarizes the study design and schedule of events (Fig 1) (Appendix A).

**g. Sample size:** The total sample size is 140 patients per drug trial- 70 patients in each arm.

**h. Study Population:** All adult patients with laboratory-confirmed SARS-CoV2 infection with mild to moderate category will be selected from the outpatient or inpatient facility in COVID-19 medical centers/hospitals. Voluntary patients will be explained about the study and if willing will sign the informed consent and be screened for eligibility.

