**Fig 1: Study Flow Diagram with Schedule of Important Study Events**

Screening of Voluntary and Consenting In-patients suffering from Mild to Moderately Severe COVID-19 for Eligibility as per Inclusion-Exclusion Criteria

3 Ayurveda formulation drug trial studies under a common protocol

(Separate study for each AYUSH 64 / Yashtimadhu / Samshamai Vati Plus)

Randomize Eligible Hospitalized Patients

(Open Label, Parallel Efficacy, Active Control Standard of Care (SOC), Two Arm Study)

Selected Ayurveda Formulation (Adjuvant) Versus SOC (Active Control)

Time Points

Clinical Assessment

Investigations

Baseline

Case Record Form (CRF), Medical History Clinical Examination, Ayurveda Assessment, Health Status (WHOQs), QoL (HR-BHF)

Diagnostic (PCR), Serology (IgM, IgG), Routine Hematology Profile, Special Assays, X-Ray Chest & Imaging, ECG

Week 4

Brief Clin Exam, Ayu Exam, Health Status (WHO- Qs) & QoL (HR-BHF Qs), Adverse Events (AEs)

Diagnostic (PCR), Serology (IgM, IgG), Routine haematology Body Profile, Special Assays

Week 8

Brief Clin Exam, Ayu Exam, Health Status (WHO- Qs) & QoL (HR-BHF Qs), Adverse Events (AEs)

Diagnostic (PCR), Serology (IgM, IgG), Routine haematology Body Profile, Special Assays

Week 12

Completion Outcome Assessment, CRF Clin Exam, Ayu Exam, WHO- Qs & QoL (HR-BHF Qs), AEs

Diagnostic (PCR), Serology (IgM, IgG), Routine haematology Body Profile, Special Assays

***Further Assessment Time Points**: (i) During Hospitalization: Daily monitored vital parameters, disease symptoms, disease progression and recovery, and investigations carried out as per protocol till DISCHARGE; Laboratory and Imaging investigations as per protocol but the study investigator and treating physician can do any additional test as per their judgment (ii)Post DISCHARGE: Daily Telephonic Contact using a special mobile phone application for any relapse or any other symptoms or complications or any other Issue (iii) Discharge: Complete all formalities as required for study completion (iv) Skip week 4 or week 8 end point evaluation within 2 weeks of DISCHARGE

The total study period is 12 weeks; Primary Efficacy is ‘Clinical Recovery’ as described in the protocol; Study participant developing severe COVID 19 or severe complication and requiring special critical support/ ICU/ ventilator support will be withdrawn from the study but followed up to record outcome;

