# 2. COVID-19 CLINICAL PROFILE

Important published research studies on COVID-19 were selected to tabulate the data on symptoms (Table 1), timelines of the course of disease (Table 2), complications (Table 3) and co-morbidity (Table 4).

COVID-19 is an acute respiratory tract infection. Though the clinical phenotype is similar to influenza, the spread and severity of illness is much more in case of COVID-19. The overall mortality of COVID-19, albeit due to respiratory complications, seems to be several folds higher than that of influenza. And unlike influenza, there is no vaccine or specific drugs to kill the virus.

Viral RNA levels have been demonstrated from upper respiratory and lung specimens. In over 90% cases, the viral RNA tests on nasopharyngeal swabs was found to be repeatedly negative at about 10 days after the onset of symptoms but the viral shedding may continue well beyond clinical recovery; median duration 20 days (range of 8 to 37 days) (9,10). In mild infections, the virus may not be detected especially if the viral RNA level in respiratory specimen is less than 106 copies/mL. Some recent studies have also shown prolonged virus shedding in stool samples.

The incubation time of COVID-19 is about 5-7 days and the infectivity is often high much before the onset of symptomatic illness (11). The infection remains asymptomatic in a substantial proportion of community and a predominant proportion of symptomatic cases will suffer from mild to moderate cases. However, asymptomatic individuals may show abnormalities in the lungs on computed tomography (CT) scans (12). It is estimated that less than 20 % cases will rapidly progress to severe stage and develop life threatening lung and systemic complications requiring critical care and often life support systems like ventilators. The overall mortality rate is about 2-3%. According to the WHO, the recovery time appears to be around two weeks for mild infections and three to six weeks for severe disease.

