**Table 2: COVID-19 TIMELINES OF THE COURSE OF DISEASE (LITERATURE REVIEW#):**

| **Study** | **Wang et al.^1^** | **Li et al.^2^** | **Huang et al.^3^** | **Zhou et al.^4^** |
| --- | --- | --- | --- | --- |
| **Site** | China | China | China | China |
| **Study type** | Retrospective  Observational  Single center | Prospective  Observational  Multicenter | Prospective  Observational  Single center | Retrospective  Observational  Multi center |
| **Nature of Site** | Hospital | Hospital | Hospital | Hospital |
| **Sample size** | 138 | 425 | 41 | 191 |
| **Time to symptoms- Median days (IQR)** | | | | |
| **Fever** | -- | -- | -- | 1 (1-1) |
| **Cough** | -- | -- | -- | 1 (1-3) |
| **Dyspnoea** | 5 (1-10) | -- | 8 (5-13) | 7 (4-9) |
| **1^st^ Hospital visit** |  | 4.6 (95%CI 4.1-5.1) | 8 (5-13) | -- |
| **Hospital admission** | 7 (4-8) | 9.1 (95%CI 8.6-9.7) | 7 (4-8) | -- |
| **Time to complications- Median days (IQR)** | | | | |
| **ICU admission** | -- | -- | 10.5 (8-17) | 12 (8-15) |
| **Mechanical Ventilation** | -- | -- | 10.5 (7-14) | 14.5 (12-19) |
| **ARDS** | 8 (6-12) | -- | 9 (8-14) | 12 (8-15) |
| **Sepsis/ Shock** | -- | -- | -- | 9 (7-13) |
| **Acute Cardiac injury** | -- | -- | -- | 15 (10-17) |
| **Acute Kidney injury** | -- | -- | -- | 15 (13-19.5) |
| **Time to outcome- Median days (IQR)** | | | | |
| **Discharge** | -- | -- | -- | 22 (18-25) |
| **Death** | -- | -- | -- | 18.5 (15-22) |
| **Recovery** | 10 (7-14) | -- | -- | -- |
| **Others** | -- | -- | -- | Viral shedding:  20 (17-24)  Severe disease:  19 (17-22)  Critical disease:  24 (22-30) |

ARDS: Acute respiratory distress syndrome. IQR: Interquartile range, CI: Confidence interval.

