# CONSENT, SELECTION, SCREENING, and ENROLLMENT

Study patients will be served on first come first serve basis as per the protocol.

Consenting and eligible patients will be enrolled as soon as possible in a COCID-19 management facility and the study intervention begun. It is important that symptomatic patients suspected for COVID-19 on clinical grounds are quickly evaluated for eligibility. It is important to enroll the patient as close to the onset of symptoms as possible. As described above, this study is dealing with patients of COVID who are ‘non-emergent’ which means mild and moderate disease (pneumonia) which does not require emergency or critical care (see section on inclusion and exclusion criteria).

An ‘Patient Information Sheet’ (Appendix F) in the language understood by the patient will be provided to each patient for study and discussion prior to enrollment. The information fact sheet will describe the overall design of the study and the rationale, benefit and side effect profile of the study drug interventions, and other aspects of the study.

Patients will be selected from the outpatient or inpatient facility in COVID-19 medical centres/ hospitals. The study will be explained to the volunteer patients and those willing to sign the informed consent (Appendix G) will be screened for eligibility as per the inclusion and exclusion criteria in the protocol.

Though it will be preferable to enrol patients with diagnosis confirmed by a positive RT-PCR assay using a nasal or throat swab in a standardized procedure, a patient with a clinical diagnosis of COVID- 19 as described below will be eligible.

Eligible patients will be enrolled using a simple randomization table (provided to the investigator) in a block of 20 patients each to either of the two study arms - SOC plus Ayurveda drug or SOC. As the target sample size is 70 patients in each arm, the first block of randomized allocation will be of 10. The study randomization will be carried out by the investigator.

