**11.2 Secondary Efficacy:**

1) Rate of patients with negative SARS-CoV-2 on nasal or throat swab in a 2-day continuous real time RT-PCR test beginning from ‘first day of clinical recovery’ (see above) or ‘Day 10 after onset of symptoms depending on whichever of the two time points is first achieved

2) Timelines (days counted from onset of illness) - normal body temperature <37◦C, absence or minimal cough (see ‘clinical recovery’ for the definition), absence of dyspnoea (respiration rate 24/minute or less on room air), onset of clinical pneumonia, pneumonia diagnosed on chest X-Ray or CT scan, time to supplemental oxygen, admit in intensive care unit, mechanical ventilation (non-invasive), mechanical ventilation (invasive), steroid use, respiratory failure, adult respiratory distress syndrome, cytokine storm syndrome, secondary infection, shock, septicaemia shock, hospital discharge, death, negative nose or throat swab confirmatory test, all-cause mortality (Time Frame: up to 28 days).

Note: In case of symptoms, the absence on improvement should be sustained for at least 72 hours or live hospital discharge, whichever comes first.

3) Proportion OF patients developing an event that reflects clinical or otherwise improvement of worsening (the events are similar to those listed under Timelines, see above)

4) Improvement on pulmonary function tests using simple ‘home expiratory spirometer’ device and peripheral pulse oximetry

5) Improvement in selected laboratory parameters: blood haemoglobin, differential and total leukocyte counts, liver enzymes, renal functions, acute phase reactants, serum IL-6 and other selected cytokines, serum muscle enzymes (CK, CPK), serum ferritin, serum d-Dimer, anti-oxidant markers, serum BNP (cardiac function)

6) Serological Protective Antibody Assay (IgM and IgG)

7) Radiological Improvement on digital chest Xray and HRCT chest

8) Drug related: side effects and toxicity, and tolerability

9) Health status: WHO QOL (Appendix M) brief, health related behaviour habit and fitness questionnaire based on visual analogue scale (See Appendix N)

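### The PCR-clearance outcome does not require a positive swab at baseline, so patients already negative at entry can be counted as cleared and the difference between arms is diluted

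*Combined protocol and SAP*

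**What the plan says.** **The outcome.** Synopsis j, Secondary Outcomes, item 1: "Rate of patients with negative SARS-CoV-2 on nasal or throat swab in a 2 day continuous real time RT-PCR test". Section 11.2, item 1, has the same definition: "Rate of patients with negative SARS-CoV-2 on nasal or throat swab in a 2-day continuous real time RT-PCR test". Testing starts on the first day of clinical recovery or on Day 10 of symptoms, whichever comes first. Item 2 in both places lists the negative swab among events timed from onset of illness. No analysis set for PCR outcomes appears there or in Section 17.2.

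**Who can enter.** The documents differ.
- Synopsis, Study Population: "All adult patients with laboratory-confirmed SARS-CoV2 infection with mild to moderate category". Inclusion criterion 1 in the synopsis and in Section 10 also asks for RT-PCR confirmation. None of these texts limits the time from that test to randomisation.
- Consent, Selection, Screening and Enrollment: a positive RT-PCR is preferred, but "a patient with a clinical diagnosis of COVID- 19 as described below will be eligible".
- Case record form (Appendix H), inclusion item 2: describes a patient with typical symptoms and an exposure history whose COVID-19 laboratory test is negative.

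**The baseline swab.** Fig 1 lists, at baseline, "Diagnostic (PCR), Serology (IgM, IgG), Routine Hematology Profile, Special Assays, X-Ray Chest & Imaging, ECG". The Schedule of Events (Appendix A, Table 1) has no RT-PCR row.

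**The concern.** A clearance rate is meant to show how many patients who carried detectable virus at the start lost it on study. A patient who is already negative at randomisation gives little information on that question but is usually counted as a success in either arm. Such patients raise both rates and pull them together, so a real effect on viral clearance would look smaller than it is.

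The time to a negative swab in item 2 has the same weakness. Its clock starts at illness onset, so the event can fall before randomisation.

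**Working it through.** **1. The plan's own figure.** Section 17.1 gives 70 per arm, and 2 × 70 = 140 agrees with the stated total. The section says that the size rests on no power calculation, and it gives no event rates or effect, so there is no planned power to reproduce.

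**2. Can a PCR-negative patient be randomised?** Yes, by three routes: a clinical diagnosis without a positive test (enrolment section), a negative test (case record form, item 2), or an earlier positive test followed by clearance before randomisation. Reconciling the eligibility texts could close the first two routes but not the third.

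**3. Dilution.** Let q be the share negative at entry, equal in both arms, all staying negative. Let p_C and p_T be the clearance rates among baseline-positive patients.
- Observed rate in an arm: p(1 − q) + q
- Observed difference: (1 − q)(p_T − p_C)

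**4. What the documents say about q.** They do not give it. Section 2 says that in over 90% of cases "the viral RNA tests on nasopharyngeal swabs was found to be repeatedly negative at about 10 days after the onset of symptoms". The same sentence goes on to a median shedding duration of 20 days, range 8 to 37, and Table 2 of the literature review gives 20 days (17–24). On the 20-day figures q is near zero. It is larger if the 10-day figure holds or if test-negative patients are enrolled.

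**5. Illustration.** Assumptions: 60% v 80% clearance among baseline-positives, 70 per arm, two-sided 0.05, no Bonferroni correction and no withdrawals. Power is Φ[(d − 1.96·se0)/se1], where d is the difference, se0 the pooled standard error and se1 the unpooled one.

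For q = 20%, all randomised:
- rates 0.6 × 0.8 + 0.2 = 0.68 and 0.8 × 0.8 + 0.2 = 0.84, so d = 0.16
- se0 = √(2 × 0.76 × 0.24/70) = 0.0722
- se1 = √((0.68 × 0.32 + 0.84 × 0.16)/70) = 0.0709
- power = Φ(0.261) = 60.3%

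For q = 20%, baseline-positives only:
- n = 70 × 0.8 = 56 per arm, d = 0.20
- se0 = √(2 × 0.7 × 0.3/56) = 0.0866
- se1 = √((0.24 + 0.16)/56) = 0.0845
- power = Φ(0.358) = 64.0%

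| q | All randomised: rates | Difference (points) | Power | Baseline-positive: n per arm | Difference (points) | Power |
|---|---|---|---|---|---|---|
| 0% | 60% v 80% | 20 | 73.8% | 70 | 20 | 73.8% |
| 10% | 64% v 82% | 18 | 67.3% | 63 | 20 | 69.2% |
| 20% | 68% v 84% | 16 | 60.3% | 56 | 20 | 64.0% |

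The power gain is 1.9 points at q = 10% and 3.7 points at q = 20%.

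**6. Other assumed rates.** With 50% v 70%, power goes from 60.4% to 63.2% at q = 10% and from 52.8% to 58.1% at q = 20%. With 90% v 98%, the 8-point difference becomes 6.4 at q = 20%, and power is 42.4% against 42.9% after restriction. The size of the difference is recovered each time; the power gain is modest at most.

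**The case against.** The strongest reply is that the confirmation requirement in the synopsis and Section 10 already supplies the missing condition. It does so only in part: a past positive test is not a positive test at randomisation, and two other texts contradict the requirement. It is also true that no denominator is written. All patients is the natural reading, but it is a reading.

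A single negative swab is weak evidence of clearance. The table of tests in Appendix O warns that viral load may be intermittent and that one negative result can mislead. So a patient negative at baseline can still fail a two-day criterion, and restriction will drop some infected patients. This stands. It is why such patients are usually, not always, scored as cleared, and why the all-randomised analysis should be kept.

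Two stronger readings are tempting and are not supported.
- A reader might set the 10-day figure beside the Table 2 admission times (median 7 days in two series, 9.1 in a third) and infer that a large share of patients is negative at entry. The 10-day sentence itself goes on to a 20-day median. Table 2 gives a first hospital visit at 4.6 days in the series with 9.1 days to admission, though another series has 8. The enrolment section asks for entry as close to onset as possible. The documents do not yield a value for q.
- A reader might count a chance imbalance in baseline-negatives as a further bias. It is ordinary sampling variation, already in the binomial variance, and the all-randomised test keeps its type I error.

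Finally, this is one of many secondary outcomes in a trial that calls itself exploratory and unpowered. That limits the weight of the point but does not remove it.

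**Conclusion.** The point holds as a gap in the outcome definition. As written, the plan lets patients who are PCR-negative at entry count towards the clearance rate, and the difference is then diluted by the factor (1 − q). With assumed rates of 60% v 80%, 20 points become 18 to 16 for q of 10% to 20%. Restriction recovers the 20 points and adds about 2 to 4 points of power.

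Both q and the clearance rates are assumptions. The calculation takes q as equal in the two arms, takes entry-negatives as staying negative, and ignores Bonferroni correction and the 15–20% withdrawal that Section 17.1 expects. If q is near zero, nothing is lost under the plan as written and nothing is lost by the change. The main gain is an outcome that measures what its purpose implies; the gain in power is secondary.

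**What to change.** 1. In synopsis j, Secondary Outcomes, and in Section 11.2, items 1 and 2 (in item 2 only the negative-swab component), define the main analysis set for PCR clearance as randomised patients with a positive baseline RT-PCR.
2. Report the number of baseline-negative patients in each arm, and keep all randomised patients as a sensitivity analysis, because one swab can be falsely negative.
3. Add the Fig 1 baseline RT-PCR to the Schedule of Events (Appendix A, Table 1) and record its date relative to randomisation. Fig 1 does not say whether this is a new swab or the confirming test listed in Section 13.
4. Reconcile the enrolment section and case record form inclusion item 2 with the synopsis and Section 10.

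The cost is a few sentences, one schedule row and a smaller denominator for this outcome (63 or 56 per arm instead of 70 at q = 10% or 20%). If the swab is taken before treatment starts, the restriction uses a pre-treatment variable and the comparison stays randomised. If the baseline PCR turns out to be only the earlier confirming test, a dated swab at entry is an added procedure.

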**10) Ayurvedic Measures: (Appendix I)**

BASELINE:

a) Prakriti

b) Clinical Features

c) Ayurvedic Disease Subsets / Stages

FOLLOW UP / MONITORING:

a) Clinical Features

b) Ayurveda examination

c) Ayurvedic Disease Subsets / Stages

**k. Medication*:**

Interventional Experimental:

i)AYUSH-64: 500 mg tablet, 2 tablets bid (twice daily)

ii)Yashtimadhu: 300 mg tablet, 2 tablets bid (twice daily)

iii)Sanshamani Vati Plus: Each tablet to contain 300 mg Guduchi plus 75 mg Pippali, 2 tablets bid (twice daily) (*Considering the *Dosha* status Ayurveda physician may change the dose.)

Concomitant:

Medication prescribed for other co-existent disease and permitted as per inclusion criteria will continue under medical supervision of the primary care physician and this will be recorded in the CRF.

